## Missing Consecutive Doses

If four or more consecutive doses of study drugs are held or otherwise not administered (i.e., the subject has not received study drug for more than 28 days), the subject will be considered intolerant of the study drug or noncompliant, whichever is more appropriate to the clinical situation. No additional study drug may be administered to such subjects without explicit permission from the Sponsor.

## Accountability of study medicinal product

The investigator is responsible for the control of drugs under investigation. Adequate records for the receipt (e.g., Drug Receipt Record) and disposition (e.g., Drug Dispensing Log) of the study drug must be maintained. Accountability will be assessed by maintaining adequate drug dispensing and return records.

Accurate records must be kept for each study drug. These records must contain the

following:

- Documentation of drug shipments (date received and quantity).
- Disposition of unused study drug not dispensed to subject.

Study drug will be dispensed according to the schedules in Table 1. A Drug Dispensing

Log must be kept current and should contain the following information:

- The date(s) and quantity of the study drug dispensed to the subject
- The date(s) and quantity of the study drug returned by the subject

All records and drug supplies must be available for inspection by the Monitor at every

monitoring visit.

Subjects will be asked to return all used drug supply containers at each visit and all unused drug supply containers at the end of treatment as a measure of compliance.

## Assessment of Compliance

At each visit, compliance with the study requirements will be reinforced.

Subject compliance with taking study drug as required will be assessed by maintaining adequate study drug dispensing records and review of the SMD. The investigator is responsible for ensuring that dosing is administered in compliance with the protocol.

Delegation of this task must be clearly documented and approved by the investigator.

It is mandatory that each administration (date and dose) be recorded in the drug diary. Subjects will be asked to return used drug containers at each visit, along with the drug diary. Returned drug containers will be counted and justified against the diary entries by study site personnel. Each verified administration will be recorded on the CRF at each visit. Unused study drug should be returned at the end of the treatment period. Under no circumstances should the treatment period for any subject extend beyond the allocated duration.

## Destruction of the study medicine

Local or institutional regulations may require immediate destruction of used study medication for safety reasons. In these cases, it may be acceptable for investigational site staff to destroy dispensed drugs before a monitoring inspection provided that source document verification is performed on the remaining inventory and reconciled against the documentation of quantity shipped, dispensed, returned, and destroyed. Written authorization must be obtained at study start up before destruction.

# Safety instruction and guidance

## Insurance and indemnity

All subjects participating in this trial will be covered for any trial medicine-related adverse effects through insurance cover to be taken out by the Sponsor.

## Adverse events and laboratory abnormalities

### Clinical adverse events

According to the ICH, an AE is any untoward medical occurrence in a subject or clinical investigation subject administered a pharmaceutical product and which does not necessarily have a causal relationship with this treatment. An AE can therefore be any unfavorable and unintended sign (including an abnormal laboratory finding), symptom, or disease temporally associated with the use of a medicinal (investigational) product, whether or not considered related to the medicinal (investigational) product. Preexisting conditions that worsen during a study are to be reported as AEs.

### Intensity

All clinical AEs encountered during the clinical study will be reported on the AE CRF.

Intensity of AEs will be graded (mild, moderate, severe) and reported in detail on the CRF.

| Mild | discomfort noticed but no disruption of normal daily activity |
| --- | --- |
| Moderate | discomfort sufficient to reduce or affect daily activity |
| Severe | inability to work or perform normal daily activity |

Note that events that are considered as life threatening should be reported as an SAE and the intensity would be reported as “severe” on the CRF.

### Drug-Adverse Event Relationship

Investigators should use their knowledge of the subject, the circumstances surrounding the event, and an evaluation of any potential alternative causes to determine whether or not an adverse event is considered to be related to the study drug, indicating "yes" or "no" accordingly. The following guidance should be taken into consideration:

- Temporal relationship of event onset to the initiation of study drug
- Course of the event, considering especially the effects of dose reduction, discontinuation of study drug, or reintroduction of study drug (where applicable)
- Known association of the event with the study drug or with similar treatments
- Known association of the event with the disease under study
- Presence of risk factors in the subject or use of concomitant medications known to increase the occurrence of the event
- Presence of non-treatment-related factors that are known to be associated with the occurrence of the event

### Serious Adverse Events (Immediately Reportable to Principal Investigator)

An SAE is any experience that suggests a significant hazard, contraindication, side effect, or precaution. It is any AE that at any dose fulfils at least one of the following criteria:

- Is fatal (results in death**; note: death is an outcome, not an event)
- Is life-threatening (Note: the term “life-threatening” refers to an event in which the subject was at immediate risk of death at the time of the event; it does not refer to an event which could hypothetically have caused a death had it been more severe)
- Requires in-patient hospitalization or prolongation of existing hospitalization
- Results in persistent or significant disability/incapacity
- Is a congenital anomaly/birth defect
- Is medically significant or requires intervention to prevent one or other of the outcomes listed above.

**The term sudden death should be used only when the cause is of a cardiac origin as per standard definition. The terms death and sudden death are clearly distinct and must not be used interchangeably.

The study will comply with all local regulatory requirements and adhere to the full requirements of the ICH Guideline for Clinical Safety Data Management, Definitions and

Standards for Expedited Reporting, Topic E2.

### Treatment and Follow-up of Adverse Events

Subjects experiencing AEs should be treated by accepted clinical procedures. If the use of medications excluded by protocol is deemed necessary, the subject may need to be discontinued from the test regimen after consultation with principal investigator. All AEs should be followed until resolved or stabilized.

### Laboratory Test Abnormalities

Laboratory test results will be recorded on the laboratory results form page of the CRF. Any laboratory result abnormality fulfilling the criteria for an SAE should be reported as such on the AE Form.

Any treatment-emergent abnormal laboratory result which is clinically significant, i.e., meeting one or more of the following conditions, should be recorded as a single diagnosis on the AE Form in the CRF:

- Is considered an SAE
- Results in discontinuation from study treatment
- Results in a requirement for a change in concomitant therapy (e.g., addition of, interruption of, discontinuation of, or any other change in a concomitant medication, therapy or treatment)

This applies to any protocol and non-protocol-specified safety and efficacy laboratory result from tests performed after the first dose of study drug, which falls outside the laboratory reference range and meets the clinical significance criteria.

The finding of an elevated ALT or AST (>3 × baseline value) in combination with either an elevated total bilirubin (>2 × ULN) or clinical jaundice, in the absence of cholestasis or other causes of hyperbilirubinemia, is considered to be an indicator of severe liver injury. Therefore, investigators must report as an AE the occurrence of either of the following:

- Treatment-emergent ALT or AST>3 × baseline value in combination with total bilirubin >

2 × ULN (of which 35% is direct bilirubin) or

• Treatment-emergent ALT or AST >3 × baseline value in combination with clinical jaundice The most appropriate diagnosis (or if a diagnosis cannot be established, the abnormal laboratory values) should be recorded on the AE CRF and reported to the principal investigator immediately (i.e., no more than 24 hours after learning of the event), either as an SAE or a non-serious AE of special interest.

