GM-CSF has the following applications in the treatment of hepatitis: (1) to treat CHB combined with IFN; (2) to treat chronic hepatitis C; (3) to be used as an adjuvant for hepatitis B vaccine; (4) to be used in hepatitis patients undergone IFN therapy with bone marrow suppression. It is safe and effective to obtain viral clearance when combined with IFN and GM-CSF. About 70% to 90% of patients may experience a decrease in total white blood cells, neutrophils, and platelet counts under IFN therapy. Among them, the decrease in neutrophil counts is the most common. The doses of IFN need to be adjusted when the decrease reaches a certain level. GM-CSF can increase the levels of white blood cells and neutrophils to help maintain the effective doses and durations of IFN, thereby improving patients’ compliance, so it is widely used in patients with hepatitis B and C during IFN treatment.

However, the combination antiviral therapy of IFN and GM-CSF is limited to clinical experience and small sample reports. How to standardize the treatment, what indicators should be used to optimize clinical practice, or how to enhance the effect of IFN? There remains a lack of large-sample multi-center standardized clinical data.

[name] from the First Hospital of Peking University designed the Y-type PEGylated recombinant human IFN alpha 2b combined with GM-CSF therapy for HBeAg-positive CHB in a multi-center, randomized, parallel controlled clinical trial in 2014. Using recombinant human Peg-IFN-α-2b (Pegabine®) as the parallel control, they preliminarily explored the treatment efficacy and safety of Peg-IFN combined with GM-CSF in HBeAg-positive CHB patients and compared the medication compliance of Peg-IFN in the two treatment plans as well, to provide a basis for standardizing the combinational therapy. The project has been reviewed by the ethics committee and multi-center clinical study is being carried out nationwide. The main target population is naïve CHB patients with HBeAg positivity, while NA-treated patients are excluded from the project.

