## Subject medication diary review

Subjects will complete a Subject Medication Diary (SMD), which the patients will bring to each study visit. The information will be reviewed by the Clinic Coordinator at each study visit. It is mandatory that each drug dose be recorded in the SMD. The patient/guardian will be instructed to record the date and dose of study drug. The person giving the medication must initial the SMD.

During the diary review, the reviewer will correct unreadable information and ask the subject to supply missing information. Reviewers will report missing doses, dose adjustments, and treatments stops or restarts on the CRF. Subject diaries will be maintained with the source documents at each site.

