## Concomitant medication and treatment

Use of any investigational drugs as a result of participation in another clinical study is prohibited during the study including the extended long-term follow-up period.

Concomitant use of any other investigational drugs (e.g., compassionate use), immunomodulatory treatments (e.g., systemic corticosteroids), growth factors (e.g., erythropoietin) or antiviral treatments with anti-HBV activity (e.g., lamivudine, tenofovir, emtricitabine, adefovir, telbivudine, systemic acyclovir, systemic famciclovir) other than those specifically allowed by this protocol are prohibited during either the treatment period or follow-up, in order to minimize the confounding effects of such treatments in determining treatment responses.

Exceptions to this are as follows:

Subjects with significant deterioration in hepatic function who permanently discontinue study drug and need to consider NA therapies in group II and group III, treatments with anti-HBV activity will not be prohibited during follow-up period.

Herbal, botanical, and other agents that are traditionally used for chronic HBV disease are discouraged.

All concomitant medications should be reported to the investigator and recorded on the appropriate electronic Case Report Form (CRF), including details of any previous anti-HBV treatment, as well as any other previous concomitant medications taken within 6 months

prior to baseline.

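### The criteria for recording a laboratory abnormality as an AE omit dose reduction or interruption of study drug and conflict with the protocol's own AE definition, so cytopenia managed only that way need not be recorded as an AE

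*Protocol*

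**What the plan says.** The section Laboratory Test Abnormalities (9.2.6 in the contents list) sends all laboratory results to the laboratory page of the CRF and then sets a narrower rule for the AE form. The rule is that a clinically significant treatment-emergent result, i.e. one "meeting one or more of the following conditions, should be recorded as a single diagnosis on the AE Form in the CRF". The conditions are:

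- "Is considered an SAE"
- "Results in discontinuation from study treatment"
- "Results in a requirement for a change in concomitant therapy", with examples that all concern concomitant medication or treatment.

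The same section adds a separate route: a rise in ALT or AST above 3 × baseline, with bilirubin above 2 × ULN or with jaundice, must be reported as an AE.

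Elsewhere the protocol foresees changes to study drug. On cytopenia under interferon, Background and Rationale states: "The doses of IFN need to be adjusted when the decrease reaches a certain level". The diary section states: "Reviewers will report missing doses, dose adjustments, and treatments stops or restarts on the CRF". Missing Consecutive Doses deals with held doses.

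Two other sections are broader than the three conditions. Clinical adverse events counts an abnormal laboratory finding as a possible AE, with no condition on the action taken. Reporting of Adverse Events requires every AE during treatment and follow-up to be reported.

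**The concern.** Lowering or skipping Peg-IFN is the response to falling counts that the protocol itself anticipates, and it is the response that the list leaves out.

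This matters more here than in most trials. Safety is part of the primary objective in the synopsis, and the safety analysis compares the three groups. The section on rhGM-CSF gives reduction of leukopenia during interferon treatment as a role of GM-CSF in this study, and the background text says that GM-CSF helps to keep interferon at effective doses. Cytopenia that forces a dose change is thus an event on which Groups II and III are expected to differ. If sites may leave it off the AE form, or if some enter it and others do not, the AE comparison between those groups is unreliable for that event. The trial is open-label, so discretion over entry is exercised with knowledge of the arm.

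**Working it through.** The protocol states no figure to reproduce; the check is a reading of the sections against each other.

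**Step 1: is the list closed?** The conditions are introduced by an i.e., so they define clinical significance rather than illustrate it. A later sentence in the section refers back to them as the clinical significance criteria.

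**Step 2: apply the list to a neutrophil fall managed only by a reduced or briefly held Peg-IFN dose.**

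| Route to the AE form | Met? |
|---|---|
| Serious | Only if the investigator judges it medically significant under the SAE definition |
| Discontinuation of study treatment | No. It applies once a stopping rule is reached (neutrophils < 0.25 × 10^9/L, or febrile neutropenia), and arguably after four or more consecutive held doses, when further drug needs the sponsor's permission |
| Change in concomitant therapy | Not by the dose change itself. Peg-IFN, and GM-CSF in Group III, are study drugs, and other growth factors are prohibited unless the protocol allows them |
| ALT/AST with bilirubin or jaundice | No; it does not concern blood counts |

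The section therefore does not require an AE entry for this event.

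**Step 3: apply the general sections to the same event.** An abnormal laboratory finding can be an AE under Clinical adverse events, and all AEs must be reported under Reporting of Adverse Events. On that reading the event is reportable. The two readings give different answers, and no text says which governs.

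**Step 4: follow-up.** Follow-up of Abnormal Laboratory Test Values ties repeat testing, at least every 2 weeks or as clinically indicated, to clinically significant abnormalities, which is the term that the list defines. An abnormality outside the list is also outside the literal wording of that rule, while scheduled treatment visits after week 4 are four weeks apart.

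**Step 5: how many patients?** Inputs: 80 to 100 patients per group (Numbers of Patients), two Peg-IFN groups, and 70% to 90% with some fall in counts under interferon (Background and Rationale).

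- Peg-IFN patients: 2 × 80 = 160 to 2 × 100 = 200.
- With any fall in counts: 0.70 × 160 = 112 to 0.90 × 200 = 180.
- With the synopsis total of 257: 257 × 2/3 ≈ 171 patients, giving 0.70 × 171 ≈ 120 to 0.90 × 171 ≈ 154, inside the same range.

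These are patients with any fall. Those whose dose is changed are a subset, and the protocol gives neither the rate of dose changes nor the count at which one is made. The range is a ceiling, not an estimate of missing AE entries.

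**The case against.** A reader might infer that a laboratory value becomes an AE only through the three conditions, so that neutropenia handled by dose change is never recorded as an AE. The protocol does not support that. The ALT/AST rule is a fourth route. The general definition and reporting duty cover laboratory findings without regard to the action taken, and the laboratory section says what should be entered without forbidding other entries. The medically significant criterion can bring in some cases, as can a stopping rule or a long run of held doses.

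A reader might also infer that interferon toxicity and the Group III versus Group II contrast will be understated in the trial as a whole. That goes too far as well. Blood counts are taken at every visit and recorded, dose changes go on the CRF, and the safety analysis section provides for laboratory data separately from AEs. Leukopenia by arm can be compared from the counts without relying on AE entries. Keeping laboratory values largely out of AE tables is a defensible choice.

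Some of the supporting text is also general: the statement on interferon dose adjustment is background, and the regimen itself is stated as fixed.

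These objections limit the finding but do not remove it. The diary section expects dose adjustments in this trial, and Missing Consecutive Doses expects held doses. If the general definition governs, the three-condition list has no effect; if the list governs, dose-modifying cytopenia is left out. The sites need to be told which. Nor do the laboratory page and the dose record replace the AE entry, since neither is stated to record that the count caused the dose change.

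**Conclusion.** The point holds as a recording gap together with an internal conflict. The laboratory criteria omit reduction, delay and interruption of study drug, so cytopenia managed only in that way need not be entered as an AE under them; the general AE sections point the other way, and six centres may differ.

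The consequence is confined to AE tabulation, including the Group III versus Group II comparison, and to the literal reach of the follow-up rule. The underlying counts and dose changes are not lost. The size is unknown: at most the 112 to 180 Peg-IFN patients with any fall in counts, and fewer to the extent that falls lead to no dose change or that sites record the event anyway.

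The conclusion rests on reading the list as a definition and on Peg-IFN doses being reduced or held for cytopenia during the trial, as the protocol anticipates. The matter should be corrected, but it does not undermine the trial's safety data as a whole.

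**What to change.** 1. Add a fourth condition to the list in Laboratory Test Abnormalities: *Results in a dose reduction, delay or interruption of any study drug*.
2. In the CRF completion instructions, link that AE to the dose-adjustment entry made at the diary review, so that the reason for each dose change can be traced.
3. Reconcile the section with Clinical adverse events and Reporting of Adverse Events by stating which rule governs AE entry of laboratory findings. The new condition alone would not settle abnormalities that lead to no action.
4. Because the follow-up rule uses the same term, confirm that its scope is as intended once the list is changed.

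The cost is one bullet, a clarifying sentence, a CRF note and more AE entries in the interferon arms, drawn from counts already taken at each visit. If the follow-up rule keeps the shared term, its repeat-testing wording would also cover these cases. The added condition concerns recording only; it sets no dose-adjustment or stopping threshold, and none is proposed here.

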### Follow-up of Abnormal Laboratory Test Values

Clinically significant laboratory abnormalities should prompt a repeat measure no less frequently than every 2 weeks or as clinically indicated, with appropriate clinical management, until they return to normal or baseline levels, and/or an adequate explanation of the abnormality is found. If a clear explanation is established it should be recorded on the CRF.

## Handling of safety parameters

### Reporting of Adverse Events

All AEs (related and unrelated) occurring during the treatment and follow-up must be reported.

### Reporting of Serious Adverse Events (immediately reportable)

Any clinical AE or abnormal laboratory test value that is serious and that occurs during the study, regardless of the treatment arm, occurring from the enrollment visit (start of study screening procedures), including follow-up must be reported to principal investigator within 1 working day of the investigator becoming aware of the event.

For initial reports of serious adverse events, investigators should record all case details that can be gathered within 1 working day on the Adverse Event CRF. A report will be generated and sent to principal investigator. A paper Serious Adverse Event CRF and Fax Cover Page should be completed and faxed immediately to principal investigator.

After informed consent, but prior to initiation of study medications, only SAEs caused by a protocol-mandated intervention will be collected (e.g., SAEs related to invasive procedures such as biopsies, medication washout, or no treatment run-in). After first study drug, all SAEs must be reported.

Unrelated SAEs must be collected and reported during the study treatment and follow-up. Related SAEs must be collected and reported regardless of the time elapsed from the last study drug administration, even if the study has been closed. Suspected Unexpected Serious Adverse Reactions (SUSARs) are reported to investigators at each site and associated IRB/IEC when the following conditions occur:

- The event must be an SAE.
- There must be a certain degree of probability that the event is an adverse reaction from the administered drug.
- The adverse reaction must be unexpected.

This study adheres to the definition and reporting requirements of ICH Guideline for Clinical

Safety Data Management, Definitions and Standards for Expedited Reporting, Topic E2.

